### Statistical analysis

We will conduct all analyses according to the intention-to-treat principle, striving to collect data from all participants. In case of missing data, data imputation techniques (multivariate imputation via chained equations) will be used. Predictive mean matching and logistic regression [86] will be used for continuous (e.g. systolic blood pressure) and categorical (e.g. MMAS-8) variables, respectively. For comparison, a per-protocol analysis will also be carried out. We will comprehensively report all missing data along with the reasons why these data are missing and explore their patterns. This information will help us to appropriately adjust future study protocols. No interim analysis is planned. Descriptive statistics will be reported as means (SD) or medians (interquartile range) for continuous variables and proportions for categorical variables. All statistical analyses will be carried out with a 5% type I error rate.

Results of the SPPA trial will be reported following the Consolidated Standards of Reporting Trials (CONSORT) 2010 statement [87, 88] and the Guidelines for reporting of health interventions using mobile phones: mobile health (mHealth) evidence reporting and assessment (mERA) checklist [36]. All analyses will be conducted with R software [89] using the basic statistical functions as well as robust functions from the package WRS2 [90] and for plotting and graphs the ggplot2 package [91].

#### Primary outcome analysis

In the primary analysis, we will compare the proportion of adherent patients according to the combined adherence endpoint after three months in the control and intervention groups using the Chi-square test. ORs and their effect sizes together with the corresponding 95% CIs will be calculated. The absolute effect size will be reported as the number needed to treat adjusted for the purposes of this trial to “number needed to remind.” To accommodate the pre/post design for the primary binary outcome, two samples McNemar test will be used [92].

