### Randomization, allocation, and concealment

Participants will be randomly assigned to either control or intervention group with a 1:1 allocation ratio. The external unblinded trial pharmacist will generate a simple randomization and allocation list with randomization numbers (patient trial codes) stratified by gender for each trial center. Freely available online software, Research Randomizer, will be used for this purpose [73]. The external unblinded trial pharmacist will provide each trial pharmacy with equal number of sequentially numbered, opaque, sealed randomization envelopes for male (blue) and female participants (red). Trial pharmacists will recruit patients in the natural, unpredictable order as they enter the pharmacy and agree to participate in the trial. After signing the informed consent form, trial pharmacists will assign a patient trial code to each participant from a randomization envelope selected in ascending order.

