### Data collection, handling, and monitoring

Trial data will be collected at Visit 1 (day of patient enrolment) and at Visit 2 (follow-up visit after three months). Table 2 provides and overview of all case report forms that will be used in the trial for data collection. Furthermore, we will actively seek and collect signals of adverse events associated with antihypertensive medication intake reported by the participants. We will also collect anonymous reasons for participation refusal and discontinuation of participation. All trial forms and materials constituting the Appendixes of the SPPA trial protocol are available in Additional file 3.

**Table 2 Tab2:** Overview of Case Report Forms in the SPPA trial

Case Report Form/Questionnaire	Details	Time Point
Case Report Form Visit 1 – PART A	Antihypertensive medication specification Mobile phone number for SMS reminders Preferred time of SMS reminder	Visit 1
Case Report Form Visit 1 – PART B	Blood pressure measurement	Visit 1
Case Report Form Visit 1 – PART C	Medication adherence measurement via MMAS-8	Visit 1
Case Report Form Visit 1 – PART D	Patient information (Sociodemographic and health information, information on mobile phone usage)	Visit 1
Case Report Form Visit 2 – PART A	Medication adherence measurement via pill count	Visit 2
Case Report Form Visit 2 – PART B	Blood pressure measurement	Visit 2
Case Report Form Visit 2 – PART C	Medication adherence measurement via MMAS-8	Visit 2

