### Sample size calculation

In the recent multinational survey, adherence prevalence in European countries was in the range of 30–76% [25]. Given the results of the latest national study reporting even lower ARs [28], we assume 30% adherence prevalence in the control group. According to a meta-analysis of randomized clinical trials, SMS reminders had the potential to double the odds ratio (OR) of medication adherence (OR = 2.11; 95% confidence interval [CI] = 1.52–2.93; *p* < 0.001) in cardiovascular patients. The weighted mean effect size was d = 0.41 (95% CI = 0.23–0.59). After adjusting for publication bias, the odds of being adherent in the group receiving SMS reminders was 68% higher than in the control group (OR = 1.68; 95% CI = 1.18–2.39) [50]. Results of the StAR trial carried out in a hypertensive population support these results, reporting an OR of 1.86 (95% CI = 1.20–2.16; *p* = 0.002) for improved adherence in patients receiving SMS reminders [84]. Therefore, we hypothesize that SMS reminders of antihypertensive medication intake can improve the proportion of adherent older patients in Slovakia from 30% to 49% given an effect size of w = 0.2 (equivalent to d = 0.4). Using a χ2 test of independence, a total of 264 patients are needed to reject the null hypothesis that the adherence proportions in both groups are equal with a power of 0.9 and alpha of 0.05. Considering approximately a 10% attrition rate, we plan to enroll 300 patients (150 in each group). Previous studies reported attrition rates of 3.2% [71], 12.8% [84], and 19.0% [70]; while the major reason for loss of participants was unwillingness or impossibility to attend the follow-up visit(s). Slovak chronic hypertensive patients are already used to regular visits of pharmacies in approximately three-month cycles. Since our trial is embedded within usual pharmaceutical care provision, we expect a lower drop-out, as in the EmPhAsIS study [85].

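### The primary chi-square test is valid, but it leaves baseline MMAS-8 unused; an adjusted logistic model would probably gain some power at almost no cost

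*Protocol article*

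**What the plan says.** All references are to the protocol article.

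- **Primary outcome analysis** compares composite adherence status after three months "in the control and intervention groups using the Chi-square test". It adds odds ratios with 95% confidence intervals, a number needed to remind, and a two-sample McNemar test meant to reflect the pre/post design.
- **Primary outcome measure (Table 3)** defines adherent as MMAS-8 of at least 6 together with a pill count rate of at least 80%, both at Visit 2.
- **Data collection, Table 2** lists "Medication adherence measurement via MMAS-8" at Visit 1 and again at Visit 2. Pill count appears at Visit 2 only.
- **Randomization, allocation, and concealment** describes a simple randomisation list "stratified by gender for each trial center". No blocks are stated.
- **Statistical analysis** commits to intention to treat and says that, where data are missing, "data imputation techniques (multivariate imputation via chained equations) will be used".
- **Sample size calculation** uses the same chi-square test: "a total of 264 patients are needed to reject the null hypothesis" of equal proportions, "with a power of 0.9 and alpha of 0.05".
- Elsewhere, baseline MMAS-8 is a subgroup factor (Subgroup analysis). Regressions of adherence on covariates including gender and pharmacy are planned (Other outcomes analyses), but that list names neither trial arm nor baseline MMAS-8.

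**The concern.** Baseline MMAS-8 is half of the endpoint definition measured three months earlier, so it is plausibly the best predictor of Visit 2 status that the trial collects. A treatment comparison that ignores a strong baseline predictor gives up power and leaves chance imbalance uncorrected. With the SD of 1.8 that the sample size section uses for MMAS-8 and 150 patients per arm, the standard error of the baseline difference is 1.8 × √(2/150) = 0.21 points. A chance gap of up to about 0.4 points would therefore be unremarkable.

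The plan shows that pre/post information was wanted. It names analysis of covariance among the analyses of systolic blood pressure and a McNemar test for the primary outcome. The McNemar route is not workable for the composite, which needs a pill count that does not exist at Visit 1. As written, the intention to use baseline adherence has no usable counterpart in the primary analysis.

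**Working it through.** **1. Reproducing the plan's figure.** Inputs from the Sample size calculation are w = 0.2, alpha 0.05 and power 0.90. For a chi-square test on 1 df, power = P(χ²₁(λ) > 3.84) with λ = N·w².

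- N = 263: λ = 263 × 0.04 = 10.52, power 0.900.
- N = 264 (even, for 1:1): λ = 10.56, power 0.901.

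The stated 264 is reproduced. With 10% attrition, 264 / 0.9 = 293.3, or 294, which is within the planned 300.

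The proportions 30% and 49% entered directly give w = 0.095 / √(0.395 × 0.605) = 0.194, slightly under 0.2. The unadjusted test then has power 0.889 at 264 and 0.924 at 300, and needs 276 for 0.90. So the starting point is about 0.89 to 0.90.

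**2. What adjustment adds.** The document does not say how strongly baseline MMAS-8, centre or sex predicts the outcome, so these inputs are assumptions. Model: a patient is adherent when Φ⁻¹(p_arm) + ρ·Z + centre + sex + error > 0. Z is standardised baseline MMAS-8, the random parts have total variance 1, and p is 0.30 or 0.49. There are six centres by two sexes, with centre SD 0.2 and sex effect ±0.15 (both set to zero in the ρ = 0 row). Other settings: simple randomisation, N = 264, 3,000 trials per setting. The Monte Carlo error on power is √(0.89 × 0.11 / 3000), about 0.6 points.

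| Assumed ρ | Chi-square | Logistic: centre, sex | Logistic: centre, sex, baseline MMAS-8 | Full model minus chi-square |
|---|---|---|---|---|
| 0 | 0.892 | 0.885 | 0.885 | -0.7 points |
| 0.3 | 0.887 | 0.895 | 0.915 | +2.8 points |
| 0.5 | 0.887 | 0.892 | 0.949 | +6.2 points |
| 0.7 | 0.891 | 0.902 | 0.976 | +8.5 points |

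Centre and sex alone move power by about 1 point or less. Nearly all the gain comes from baseline MMAS-8. A separate simulation at N = 270 gave the same pattern: about 0.90 unadjusted, against 0.91, 0.94 and 0.97 at ρ = 0.3, 0.5 and 0.7.

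**3. Treating the endpoint as two components.** The model above gives the composite a single latent scale, which may flatter the gain because pill count has no baseline value. A second model used separate MMAS-8 and pill-count components and a nine-level baseline score (N = 270, correlation 0.3 between components, correlation 0.1 to 0.2 between baseline MMAS-8 and pill count).

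| Assumed correlation, baseline with Visit 2 MMAS-8 | Chi-square | Adjusted |
|---|---|---|
| 0.3 | 0.893 | 0.901 |
| 0.5 (two settings) | 0.904; 0.893 | 0.910; 0.918 |
| 0.6 | 0.905 | 0.929 |
| 0.7 | 0.907 | 0.945 |

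The gain is then about 1 to 4 points. If baseline MMAS-8 correlates 0.5 with pill count, it is 5 to 8 points.

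**4. Validity.** With no treatment effect, rejection rates under simple randomisation were 0.049 to 0.057 for the chi-square and 0.051 to 0.057 for the fully adjusted model. Both are near 0.05, given a Monte Carlo error of about 0.4 points.

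**5. Pooling over imputations.** An illustration used 150 per arm, 10% missing, 20 imputations and about 30% versus 49%. Rubin's rules on the log odds ratio give OR 2.23 (95% CI 1.35 to 3.70), p = 0.0018. On the risk difference they give 0.188 (SE 0.059), p = 0.0014. Combining the chi-square statistics themselves by the D2 rule gives p = 0.0017.

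**The case against.** The strongest reply is that nothing here is wrong. A two-sample chi-square is a valid test of equal proportions, it keeps its size, and the sample size was computed for it. A more efficient model is then a preference. That reply stands as far as it goes, and it limits this point to an improvement.

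A reader might infer three stronger things, none of which the document supports:

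- **That stratified allocation makes the unadjusted test improper.** The list is described as simple randomisation with no blocks, so balance within strata is not forced and the usual argument hardly applies. Even with permuted blocks, rejection in the settings with prognostic strata was 0.046, at most slightly conservative.
- **That the primary result cannot be pooled over imputations.** Rubin's rules do not apply to a raw chi-square statistic, but the planned odds ratio pools on the log scale and the D2 rule handles the statistics. The pooling rule may also sit in an analysis plan that is not shown.
- **That the trial is underpowered because of this choice.** It was sized for the unadjusted test. At the bias-adjusted OR of 1.68 cited in the sample size section, 30% becomes 41.9% (odds 0.4286 × 1.68 = 0.72; 0.72 / 1.72). Unadjusted power is then about 0.53 with 135 per arm. The single-scale model raises it to only 0.59 to 0.69 at correlations of 0.5 to 0.7, so adjustment does not cure a smaller true effect.

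It is also fair to say that baseline MMAS-8 is not ignored altogether, since it is a subgroup factor. That use gives no adjusted overall treatment effect.

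**Conclusion.** The point holds as an efficiency improvement. The chi-square test is sound, but the plan collects an earlier value of an endpoint component and has no workable way of using it in the primary comparison. At the design alternative, adjustment changes power of about 0.89 to 0.90 by about -1 to +9 points over assumed latent correlations of 0 to 0.7. The gain is about 1 to 4 points if baseline MMAS-8 predicts pill count only weakly. The size rests wholly on a correlation that the document does not give; the direction is probably favourable. Adding sex and centre matters little for power and is included because they are the randomisation factors.

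**What to change.** In Primary outcome analysis, before database lock:

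- Make the primary analysis a logistic regression of Visit 2 composite status on arm, baseline MMAS-8 (continuous), sex and centre, with small centres merged.
- Pool the log odds ratio over the planned imputations by Rubin's rules.
- From the same model, report a standardised risk difference with 95% CI as the basis for the number needed to remind.
- Keep the unadjusted chi-square and crude odds ratio as supportive.
- Remove the McNemar test for the composite, or confine it to the MMAS-8 component, which is measured at both visits.

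The cost is a short wording change, with no extra patients, visits or data. The small downside is that the adjusted odds ratio is conditional and will differ slightly from the crude one, which is why the standardised risk difference should stand beside it.

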### Outcome measures

#### Primary outcome measure

Our primary outcome is the proportion of adherent patients in the intervention group after three months of receiving SMS reminders of medication intake. For these purposes, we will assess patients’ adherence via combined adherence endpoint consisting of self-reported medication adherence measured via MMAS-8 and pill count rate (%).

The eight-item MMAS questionnaire, on which the MMAS-8 is based, evaluated hypertensive patients. It showed good reliability (α = 0.83) as well as sensitivity (93%) and specificity (53%) in the identification of lower versus higher adherence to antihypertensive medication. Additionally, the association between MMAS-8 and blood pressure control was proved statistically significant (*p* < 0.05) [19]. Each question aims at assessing a specific medication-taking behavior, either intentional or unintentional. The first seven questions have dichotomous answers (yes/no), whereas the last question offers a five-point Likert response. The range of the scores is from 0 to 8 with 0 being low adherence and 8 indicating full medication adherence [19, 74].

Pill count is a simple objective indirect measurement of patients’ adherence to medication intake [75]. AR will be calculated using the following equation:$$ \mathrm{A}\mathrm{R}\left(\%\right)=\left(\frac{\mathrm{No}.\mathrm{of}\;\mathrm{pills}\;\mathrm{actually}\;\mathrm{taken}}{\mathrm{No}.\mathrm{of}\;\mathrm{pills}\;\mathrm{that}\;\mathrm{should}\;\mathrm{have}\;\mathrm{been}\;\mathrm{taken}}\right)\times 100 $$

No specific guidelines exist on how to assess medication adherence [76]; therefore, we based our categorization of a patient as being “adherent” or “non-adherent” on the previous literature and expert opinions. Our study team agreed that a patient at the end of the trial will be considered as either “adherent,” having MMAS-8 ≥ 6 [19] and pill count rate ≥ 80% [77], or “non-adherent” if one or both of the previous conditions are not met. Table 3 contains details on our primary outcome measure.

**Table 3 Tab3:** Primary outcome Combined adherence endpoint

Level	
Domain	Combined medication adherence
Specific measurement variable	Adherence status (dichotomous) adherent: MMAS-8 score ≥6 and pill count rate ≥80% non-adherent: MMAS-8 score <6 and/or pill count rate <80%
Analysis Metric	Final value (Visit 2)
Method of aggregation	Proportion of adherent patients (%)

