Time point of measurement	At Visit 2 (follow-up visit after 3 months of intervention period)

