#### Patients’ satisfaction with SMS reminders

First, we will analyze the psychometric quality of the questionnaire items. Cronbach’s alpha, McDonalds’s hierarchical omega, as well as Mokken scale analysis [95] will be used to find out if all items have sufficient quality to be included in the final scale. In case of significant deficiencies, item(s) will be excluded. Second, using the final scale, we will analyze the impact of patient satisfaction level on the change of adherence and systolic blood pressure values via multivariate linear regression, controlling for impact of sex, age, education, etc. This way we strive to find out if the overall satisfaction level of patients is a significant predictor variable for the change in ARs and/or systolic blood pressure values.

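### The pre/post McNemar test on the composite primary outcome cannot be computed, because pill count is collected only at Visit 2 and the composite has no baseline value

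*Protocol article*

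**What the plan says.** All references are to the protocol article.

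- **Primary outcome measure.** Adherent status is defined as follows: "having MMAS-8 ≥ 6 [19] and pill count rate ≥ 80% [77], or “non-adherent” if one or both of the previous conditions are not met". The status is assigned once: "a patient at the end of the trial will be considered as either “adherent" or not. Table 3 gives the analysis metric as "Final value (Visit 2") and the time point as "At Visit 2 (follow-up visit after 3 months of intervention period").
- **Data collection, handling, and monitoring, Table 2.** The entry "Medication adherence measurement via pill count" appears once, on the Visit 2 form, Part A. The entry "Medication adherence measurement via MMAS-8" appears twice, for Visit 1 and Visit 2. The other Visit 1 parts hold medication and SMS details, blood pressure and patient information.
- **Primary outcome analysis.** The primary analysis is a chi-square comparison of the arms after three months, with odds ratios and a number needed to remind. The paragraph then ends: "To accommodate the pre/post design for the primary binary outcome, two samples McNemar test will be used".
- **Patients' satisfaction with SMS reminders.** Satisfaction is examined as a "significant predictor variable for the change in ARs" and/or in systolic blood pressure.

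**The concern.** A McNemar test works on pairs. Each patient needs the same binary status before and after, and a two-sample version compares those paired changes between the arms. The primary outcome has only an after value, so the article names an analysis that its own data schedule cannot support.

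Anyone who tries to run it must invent a baseline status after the fact. The obvious candidate is MMAS-8 of at least 6 alone. The composite adds a second condition to that, so it can never be easier to meet, and patients whose behaviour has not changed can be counted as having declined. A reported within-arm change on the primary outcome would then be partly an artefact of definition. The role of the test beside the chi-square is also not stated.

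**Working it through.** **1. The plan's own figure.** Sample size calculation gives 264 patients for a chi-square test with w = 0.2, alpha 0.05 and power 0.9. With one degree of freedom the noncentrality is N × w² = 264 × 0.04 = 10.56, and the power is 0.901. The smallest N reaching 0.90 is 263, or 264 for equal arms. The figure reproduces. It depends only on the two arms' Visit 2 proportions and makes no use of a baseline status.

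**2. What the McNemar test needs, against what is collected.**

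| Component | Visit 1 | Visit 2 |
|---|---|---|
| MMAS-8 ≥ 6 | collected | collected |
| Pill count ≥ 80% | not collected | collected |
| Composite status | not defined | defined |

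This does not rest on Table 2 alone. Table 4 gives Visit 2 as the only time point for the pill-count adherence rate, and the analysis section for that outcome says the same. The text under Exclusion criteria explains that the pills to be counted come from the package collected on the recruitment day and usually started the next day. No counting period therefore precedes Visit 1.

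**3. Can the baseline status be recovered?**

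- A Visit 1 MMAS-8 below 6 would already make a patient non-adherent. A score of 6 or more leaves the status open, so the adherent row of the paired table stays empty.
- The chained-equation imputation in Statistical analysis cannot help. Baseline pill count is unobserved for every patient by design, so no observed values exist from which to impute it.

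**4. Effect of an MMAS-8-only baseline on within-arm change.** The documents do not give the rates needed, so these are assumptions. Let a be the proportion with MMAS-8 ≥ 6 at both visits in an arm where nothing changes, and c the proportion of those with pill count ≥ 80%. The apparent change is a × c − a. Fixing a × c at 0.30, the control rate the article assumes:

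| a | c | Composite at Visit 2 | Apparent change |
|---|---|---|---|
| 0.30 | 1.00 | 0.30 | 0 points |
| 0.40 | 0.75 | 0.30 | −10 points |
| 0.50 | 0.60 | 0.30 | −20 points |
| 0.60 | 0.50 | 0.30 | −30 points |

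**5. Effect on the between-arm comparison of change.** Randomisation gives both arms the same expected baseline a. With the planned Visit 2 rates, the difference in change is (0.49 − a) − (0.30 − a) = 0.19 for every a, which is the planned effect. With equal Visit 2 rates it is zero. On the difference scale the mismatch cancels in expectation.

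**The case against.** The strongest reply is that little depends on this sentence. The article introduces the chi-square test as the primary analysis, sizes the trial on it, and defines the outcome as a Visit 2 value. All three agree on one primary test, and that test can be run as planned. This stands, and it limits the severity.

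Three stronger readings are tempting, and the documents do not support them.

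- **Two competing primary tests.** A reader might infer that the article offers a second route to a primary p-value. Nothing says the McNemar test can decide the trial. What can fairly be said is that its role is unlabelled.
- **A false decline comparable to the 19-point effect.** A reader might set the within-arm loss in step 4 against the planned difference of 49% − 30%. The first is a change within an arm on assumed rates, and the second is a difference between arms. Step 5 shows that the artefact is common to both arms.
- **The same error in the satisfaction analysis.** A reader might infer that a change in ARs is equally impossible. The article defines AR by pill count under Primary outcome measure, but Subgroup analysis applies the term to baseline self-report on MMAS-8. On that reading a change can be computed, so the term is ambiguous and the analysis is not shown to be impossible.

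It could also be said that MMAS-8 alone was meant, or that a separate analysis plan settles the matter. The sentence names the primary binary outcome, which is the composite. An analysis plan could drop or redefine the test, but it could not supply a measurement that was never taken.

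**Conclusion.** The point holds in a narrow form. As written, the pre/post McNemar test on the composite cannot be computed, because the composite has no Visit 1 value. This follows from the article's own schedule and needs no assumption.

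If an MMAS-8-only baseline were improvised, within-arm change would be biased downwards wherever some patients with MMAS-8 ≥ 6 fall short on pill count. The size, 0 to 30 points in the table, rests on assumed values of a and c with the composite held at 30%. The cancellation between arms rests on randomisation and on measuring change as a difference in proportions. The Visit 2 chi-square test and the sample size of 264 are not affected.

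Severity: moderate.

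**What to change.** 1. Delete the McNemar test on the composite. Alternatively, restrict it to MMAS-8 ≥ 6 at both visits, which is computable, and label it supportive.
2. State that the between-arm chi-square test of Visit 2 composite status is the single primary test.
3. To use the baseline information that exists, add a supportive logistic regression of Visit 2 composite status on arm, adjusted for baseline MMAS-8. It should stand beside the chi-square and not replace it: a chi-square test takes no covariate, and the sample size was set for that test.
4. In the satisfaction analysis, state whether ARs means MMAS-8, for which a change can be computed, or pill count, for which only the Visit 2 value exists.

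Items 1, 2 and 4 are changes of wording. Item 3 costs one extra model and a conditional odds ratio to report and explain beside the unadjusted one. None of them changes data collection or the number of patients. Trial status says recruitment is under way, and the statistician receives data only after database lock, so all four can be settled before outcome data are seen.
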